**Methods:**

A total of 81 stroke patients will be recruited and randomly assigned to control, fixed reward, or probabilistic reward groups at a ratio of 1:1:1 using a randomized number table method. Participants will undergo 10 days of daily hand motor function rehabilitation training, with sessions lasting 20 min each. The training will involve pegboard tests and box and block tests. Control group participants will receive standard training, while fixed reward group members will receive monetary incentives for completing tests, and probabilistic reward group members will have the chance to win monetary rewards through a lottery box. Rehabilitation motivation and motor performance and functional near-infrared spectroscopy brain imaging will be conducted at designated time points. The primary outcome measure is the stroke rehabilitation motivation scale, and the second outcome measures include motor performance, simple test for evaluating hand function, motivation and pleasure scale self-report, and Pittsburgh rehabilitation participation scale.

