Previous studies have explored the effectiveness of fixed reward-based training in stroke rehabilitation, but there remains a need for comparative research to determine which approach—fixed or probabilistic reward—is more sensitive and efficient. The optimal types and delivery methods of rewards in stroke rehabilitation remain underexplored. Addressing this gap in the literature will provide valuable insights into optimizing stroke rehabilitation protocols and ultimately improving patient outcomes. This study aims to compare the efficacy of fixed and probabilistic reward strategies in enhancing motor learning ability and rehabilitation motivation in stroke patients, and seeks to inform the development of evidence-based rehabilitation protocols and improve patient outcomes following stroke.

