### Sample size

The statistical software G-power (Heinrich Heine University Düsseldorf, Dusseldorf, Germany) was utilized to ascertain the sample size, with an alpha value set at 0.05, power at 0.95. By employing Cohen’s d using data extracted from a prior study by Chen et al. (15), we ascertain the mean discrepancy between groups to be 2.34 (27.54–25.2), with a pooled standard deviation approximating 3.47. Acknowledging the discrepancy in sample sizes between the two groups, the effect size is computed to be 0.674. With these parameters, the calculated sample size per group was determined to be 23 participants, summing up to 69 participants across three groups. Anticipating a dropout rate of 15%, the final sample size was adjusted, necessitating 27 participants per group, resulting in a total sample size of 81 participants.

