### Outcome assessment

The components of the assessment include basic information (gender, age, duration of illness, medication history, etc.), motivation, motor performance and objective assessments. The main assessments focus on motivation and motor performance. Comprehensive video recordings of each training session will be subjected to meticulous analysis to evaluate daily motor performance. Rehabilitation motivation evaluations and functional near-infrared spectroscopy (fNIRS) measurements will be conducted at designated time points (Table 1).

**Table 1 tab1:** Recommended content for the schedule of enrolment, interventions, and assessments.

	Study period						
	Enrolment and assessment	Allocation	Training			Follow-up	
Timepoint	−D_1_	0	D_1_	D_2_–D_9_	D_10_	D_14_	D_28_
Enrolment							
Eligibility screen	X						
Informed consent	X						
Allocation		X					
Interventions							
Control group							
Fixed reward group							
Probabilistic reward group							
Assessments							
SRMS	X		X		X	X	X
MAP-SR	X		X		X	X	X
PRPS	X		X		X	X	X
Motor performance	X		X	X	X	X	X
fNIRS	X		X		X	X	X

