### Statistical analysis

Categorical variables like gender and affected side will be presented as percentages and compared using the chi-square test. Continuous variables will undergo normality assessment with the Shapiro–Wilk test and variance homogeneity examination with Levene’s test. One-Way ANOVA will compare motivation among groups before and after training, followed by Tukey’s HSD test for *post hoc* comparisons. The repeated measures ANOVA was performed to analyze changes in rehabilitation motivation scales data and average time spent in pegboard test and BBT in the three groups. Non-normal or heterogeneous data will be analyzed using the Kruskal-Wallis test, with *post hoc* tests conducted using Dunn’s test. Normal data will be presented as mean ± standard deviation, while non-normal data will be presented as median and quartiles. The significance level (P) for hypothesis testing will be set at 0.05.

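### The sole primary outcome, SRMS, has two planned analyses at an undivided 0.05, and the protocol does not say which one decides

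*Protocol article*

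**What the plan says.** The Abstract names one primary outcome: "The primary outcome measure is the stroke rehabilitation motivation scale". No primary time point is given. Under Outcome assessment, "Rehabilitation motivation evaluations and functional near-infrared spectroscopy (fNIRS) measurements will be conducted at designated time points"; Table 1 lists SRMS at five of them: before allocation (−D1), on the first and last training days (D1, D10), and at two follow-up visits (D14, D28).

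The Statistical analysis section gives motivation two analyses:

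- A comparison of the groups at separate times: "One-Way ANOVA will compare motivation among groups before and after training". Pairs of groups are then compared by Tukey's HSD.
- An analysis over time: "The repeated measures ANOVA was performed to analyze changes in rehabilitation motivation scales data". The same method is applied to the pegboard and Box and Block data.

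Non-normal or heterogeneous data go to Kruskal-Wallis with Dunn's test. The section closes with one level: "The significance level (P) for hypothesis testing will be set at 0.05". There is no order between the two analyses, no division of the level, and no statement of which result the conclusion will rest on.

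**The concern.** The two analyses ask related but different questions of the same scale. The one-way ANOVA asks whether the groups differ at a post-training visit. The repeated-measures ANOVA asks whether their course over time differs. Each gets its own 0.05, and a chance finding can arise in one without the other.

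Tukey's HSD and Dunn's test deal with the three pairs of groups inside one analysis. Neither reaches across to the other analysis. If the choice of the decisive analysis is left until the results are known, a positive conclusion could rest on whichever one crossed 0.05. The true false-positive rate for the primary outcome would then exceed the level in the Statistical analysis section, and the level assumed in the Sample size section ("with an alpha value set at 0.05, power at 0.95").

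**Working it through.** **Inputs from the protocol.** Three groups of 27 (Sample size; Randomization); level 0.05 (Statistical analysis); five SRMS visits (Table 1).

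**Assumed.** The protocol gives no within-person correlation for SRMS, so a range was used. Data are normal with equal correlation between all visits, and there is no true group difference at any visit. The before-training ANOVA is a baseline comparison, not an efficacy test, and is left out throughout.

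**Step 1: bounds that need no correlation.** For two tests each at 0.05, the chance that at least one is significant under no effect lies between 0.05 (complete overlap) and 0.05 + 0.05 = 0.10 (no overlap). If they were independent it would be 1 − (1 − 0.05)² = 1 − 0.9025 = 0.0975.

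**Step 2: where this pair falls.** The plain reading pairs the one-way ANOVA at D10 with the group-by-time interaction from the five-visit repeated-measures ANOVA. Simulating 40,000 null trials per correlation:

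| Correlation | D10 ANOVA alone | Interaction alone | Either significant |
|---|---|---|---|
| 0.3 | 0.0503 | 0.0491 | 0.0906 |
| 0.5 | 0.0502 | 0.0501 | 0.0930 |
| 0.7 | 0.0513 | 0.0490 | 0.0951 |
| 0.9 | 0.0474 | 0.0504 | 0.0945 |

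The simulation error is about √(0.093 × 0.907 / 40,000) ≈ 0.0015. A smaller run (8,000 trials each at correlations 0.4, 0.6 and 0.8) gave 0.092 to 0.097. Each test alone reproduces the stated 0.05; the pair comes close to the independence value. Relative to 0.05, the first run gives 0.0906/0.05 = 1.8 to 0.0951/0.05 = 1.9 times.

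**Step 3: sensitivity.** With 23 per group, the number before the dropout allowance, the rates are 0.092 and 0.095 (correlations 0.5 and 0.7). If the repeated-measures analysis uses only one pre-training and one post-training visit, so that the interaction is a comparison of change, the rate is 0.090 to 0.098.

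**Step 4: what wider readings would add** (correlations 0.3 to 0.9):

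- D10 ANOVA, interaction, or repeated-measures group effect: 0.108 to 0.125.
- One-way ANOVA at any of D10, D14 and D28, or the interaction: 0.128 to 0.165.
- One-way ANOVA at any of the four post-allocation visits, or either repeated-measures term: 0.138 to 0.208.

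These need tests that the Statistical analysis section does not list, or does not list clearly.

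**Step 5: after the fix.** One named test returns the rate to about 0.05 (0.047 to 0.051 for the D10 ANOVA in Step 2). Two primary tests at 0.025 each are bounded by 0.025 + 0.025 = 0.05.

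**The case against.** The strongest reply is that this is a condensed article. A full protocol or SAP may name the decision test, and setting a time-course model beside an endpoint comparison does not declare both confirmatory. That stands to this extent: the 0.09 to 0.10 is conditional on either analysis being allowed to claim success. It does not dispose of the point, because the article is not merely silent. It assigns two tests to its one primary outcome and attaches one undivided level to hypothesis testing.

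A reader might infer that the error is up to four times nominal, counting a one-way ANOVA at every visit (Step 4). The text does not support that. It limits the one-way ANOVA to before and after training. Table 1 puts D1 under training and D14 and D28 under follow-up, so D10 is the natural post-training visit. The repeated-measures analysis is described as one of changes, which does not point to the group main effect.

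A reader might also infer, from the aim "This study aims to compare the efficacy of fixed and probabilistic reward strategies in enhancing motor learning ability and rehabilitation motivation in stroke patients", that three-group tests miss the trial's question. That goes too far. Tukey's or Dunn's procedure tests fixed against probabilistic reward directly. The Study design section frames the purpose as different reward strategies in a design with a control arm, so a difference from control is within scope. Whether to elevate one contrast is a trade-off, not an error. Nor does the protocol plan separate tests of the seven SRMS dimensions; it only describes them.

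**Conclusion.** The concern holds in limited form. As written, the plan does not hold 0.05 for SRMS if either analysis can carry the conclusion: the rate is about 0.09 to 0.10 on the plain reading. That rests on 27 per group, normal data, equal correlation between visits, and an assumed correlation of 0.4 to 0.8; results at 0.3 and 0.9 are much the same. The bound of 0.10 for two tests needs none of the distributional assumptions beyond each test holding its own level. Higher rates apply only if D14 and D28 also count as post-training visits for the one-way ANOVA, or other additional tests such as the repeated-measures group effect are used.

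**What to change.** Before unblinding, name one decision analysis for SRMS: a comparison of the three groups at one stated visit, for example the end of training (D10), adjusted for the baseline SRMS already collected, at two-sided 0.05. Follow it with Tukey-adjusted pairwise comparisons that include probabilistic versus fixed reward. Label the repeated-measures ANOVA and the other visits as supportive. If the rank-based fallback is kept, say that it replaces the decision analysis and is not run in addition to it.

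If both analyses are to stay primary, test each at 0.025 and say so; this lowers the power of each.

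Naming one analysis changes wording only: no extra patients, visits or measurements. The small downside is that an effect seen only in the repeated-measures analysis, or only at another visit, becomes supportive.

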## Discussion

Stroke-induced motor impairments pose significant challenges to patients’ quality of life and independence, necessitating effective rehabilitation strategies. As highlighted in the introduction, stroke survivors often experience difficulties in motor learning due to neuroplastic changes in the brain, coupled with motivational barriers that hinder active participation in rehabilitation activities (20, 21). The incorporation of reward strategies, such as positive reinforcement and goal-setting, aims to address these challenges by enhancing motivation and engagement in therapy sessions (22).

Previous studies have consistently demonstrated the efficacy of motivational interviews and reward-based training in bolstering the rehabilitation motivation of individuals with neurological injuries. For instance, findings from various intervention studies revealed a significant positive effect of motivational interviewing on patient engagement and adherence to rehabilitation programs (23–25). Similarly, comparing traditional rehabilitation approaches with reward-based training found that participants in the reward group exhibited higher levels of motivation and persistence in completing motor tasks (26). Furthermore, Studies have elucidated the neural mechanisms underlying the influence of rewards on motivation, highlighting the activation of dopaminergic pathways and the striatum during reward anticipation, which in turn enhances motivation and learning processes (27). Collectively, these findings underscore the importance of incorporating motivational strategies and reward systems into neurorehabilitation protocols to optimize patient outcomes and facilitate recovery.

Earlier studies demonstrated that reward alone did not enhance the learning rate in the VMR task, whereas reward combined with punishment not only accelerated the learning rate but also increased the learning extent (28, 29). Nikooyan et al. suggested that reward feedback alone can drive motor adaptation (without increasing the rate beyond that of the control group), and the combination of reward and sensory feedback accelerates learning (30). It was also supported that reward alone boosts or accelerates learning speed in sequence learning paradigms. The participants with monetary incentives have a higher learning rate in a discrete motor sequence task because the reward enhances motivation (31). Additionally, Sebastian Sporn et al. dissociated the effects of different types of rewards, namely, performance feedback and monetary incentives, through a novel motor task, and the results demonstrated that monetary incentives alone rapidly shortened movement time, whereas feedback after correct responses primarily improved learning-related movement time performance. Importantly, pairing both monetary incentives and feedback after correct responses enhanced movement time performance and improved fusion of movements (12). The majority of studies investigating the impact of rewards on motor learning mentioned above were conducted in healthy participants, employing fixed reward paradigms. It wasn’t until 2017 that, in a visuomotor rotation-based reaching task utilizing a robotic arm, the reward group of chronic stroke patients exhibited superior adaptation and readaptation compared to the neutral group, and finally, the reward group showed greater retention. Quattrocchi et al. were the first to provide evidence that reward and punishment can augment motor adaptation in stroke patients (32). This finding was corroborated by a recent study which was also conducted in stroke patients (33). However, the rewards utilized in these investigations remained fixed. To date, there is still a lack of randomized controlled trials examining the effects of fixed versus probabilistic rewards on motor rehabilitation in stroke patients. The study we are undertaking aims to address this gap.

The comparison between fixed and probabilistic reward strategies provides valuable insights into their respective efficacy in promoting motor learning and rehabilitation motivation among stroke patients. This study will contribute to the growing body of evidence on the effectiveness of reward-based interventions in stroke rehabilitation. By elucidating the differential impacts of fixed and probabilistic rewards on patient outcomes, this research informs the development of tailored rehabilitation protocols that optimize motivation and motor learning outcomes in stroke survivors. The novelty of this study lies in its comparative approach, which directly assesses the relative effectiveness of fixed versus probabilistic reward strategies in stroke rehabilitation. In addition to its clinical implications, this study contributes to theoretical models of motivation and learning in rehabilitation settings. By elucidating the mechanisms underlying the effectiveness of reward-based strategies, such as reinforcement schedules and expectancy theory, this research may enhance our understanding of the psychological factors that influence patient engagement and adherence to rehabilitation programs.

Overall, this study underscore the importance of integrating motivational strategies into stroke rehabilitation protocols to enhance motor learning ability and rehabilitation motivation. By identifying the most effective reward strategies for stroke patients, this research has the potential to inform clinical practice and improve the effectiveness of rehabilitation interventions.

## Ethics statement

The studies involving humans were approved by Ethics Committee of Shanghai Second Rehabilitation Hospital of Shanghai. The studies were conducted in accordance with the local legislation and institutional requirements. The participants provided their written informed consent to participate in this study.
